**Methods::**

This randomized, controlled, evaluator-blind, two-arm, parallel clinical trial will include 90 outpatients with chronic low back pain recruited from the First Hospital of Nanping City, Fujian Province. The patients were randomly assigned to the intervention group (Baduanjin exercise training) and the control group (not receiving any special exercise training) at a ratio of 1:1. Patients in the intervention group will receive Baduanjin exercise training 3 times a week for 24 weeks. The 2 groups received a 4- week follow-up observation at 24 weeks. The main result from the intervention before intervention to 24 weeks later, and the follow-up of 4 changes the visual analog scale score at weeks, and by independent t are tested groups. It will also review the Pain-related disability index, The Quebec Back Pain Disability Scale, Health-related quality of life, Roland Morris (Roland Morris) Disability Questionnaire, Overall Perceived Effect (OPE) and safety Compare. Cost data for cost-benefit and cost-benefit analysis will be collected.

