### Research design

2.2

This study is a randomized, controlled clinical trials, will conform to the conditions of 90 participants according to the proportion of 1:1 were randomly divided into intervention group (Baduanjin group) and control group (not exercise training group). All the members of the intervention group received Baduanjin training 3 times a week for 24 weeks. All cases in the control group did not receive any exercise training for 24 weeks. Primary and secondary outcomes will be measured at baseline, 8, 16 and 24 weeks after intervention, and the next 4 weeks. The research design flowchart is shown (Fig. 1). The research protocol was described in accordance with “ SPIRIT 2013 statement: defining standard protocol items for clinical trials ”.^[29]^

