### Inclusion criteria

2.3

1.Male and female subjects aged 19 to 70 years;2.Pain that lasts at least 3 months;3.At the time of inclusion, pain and discomfort were over 40 mm on the 100 mm Visual Analog Scale (VAS);^[30]^4.Normal intelligence, able to communicate and communicate, able to complete the basic movements of Baduanjin;5.Voluntarily provide written informed consent and are willing to follow instructions related to the trial.

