### Outcome indicators

2.16

#### 
Primary endpoint

2.16.1

The main outcome of our study will be the change in VAS score of pain from baseline to the completion of the intervention (week 24).^[30]^ Patients will quantify pain intensity by marking the most relevant points anchored by 2 descriptors on a 100 mm horizontal line: 100 for ”most imaginable pain” and 0 for ”no pain”.

#### 
Secondary ending

2.16.2

Pain-related disability index is used to measure general disability related to pain.

The Pain Disability Index is a widely used and researched tool for measuring pain-related disability, especially in chronic low back pain, fibromyalgia, cancer, or chronic generalized pain.^[33]^ Pain Disability Index is mainly composed of 7 projects, including family responsibilities, entertainment, social activities, occupation, sexual behavior, self-care, and life support activities. Each item is evaluated using a numerical score scale of 0 to 10, where 0 means no disability, 10 means the highest disability, and the total score is 70 points. The higher the score, the more the pain interferes with daily activities. Pain Disability Index is easy to understand and is an effective and reliable tool.

The Quebec back pain disability scale is used to measure disability related to specific back pain.^[34]^

The Quebec back pain disability scale is mainly used to assess the difficulty of various daily activities patients with low back pain. These activities are mainly divided into 6 areas, across a total of 20 questions: bed rest (question 1–3), sitting (question 4–6), walking (question 7–9), exercise (question 10–12), bending over (question 13–16) and carrying heavy objects (questions 17–20). Each question has 6 options, with a score of 0 to 5. A score of 0 means no difficulty, a score of 5 means unable to complete, and a higher score means more severe dysfunction. The total score is 100 points.

Measure the health-related quality of life through the SF-36 Health Survey.^[35]^

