### Statistics

2.21

All data are statistically analyzed using Statistical Product and Service Solutions (SPSS©), version 20.0 (IBM Corp., Armonk, NY, USA). Continuous variables will be mapped by the mean and its SE (normal distribution) or median and IQR (non-normal distribution). Categorical variables will be delineated as a frequency or percentage. The baseline characteristics between the comparison groups will be compared using the *t* -test or Mann-Whitney *U* test for continuous variables, while Pearson χ^2^ or Fisher exact test will be employed to compare categorical variables. The analysis of primary or secondary results will be established with the intent to treat principle, and missing data will be interpolated using multiple imputation methods. Student's *t* test or Mann-Whitney *U* test will be used to analyze the difference between the intervention group and the control group at each time period (8 weeks after the intervention, 16 weeks, and 24 weeks or 4 weeks of follow-up). In the safety analysis, the total adverse event rate and adverse event rate associated with Baduanjin were tested by Pearson χ^2^ or Fisher's exact test.

Primary analysis: treatment efficacy. The statistical analysis of primary and secondary results will be based on treatment principles. The effect of the intervention on pain distress, pain intensity, function, disability, and overall sensory effects will be determined using a linear mixed model (random intercept and fixed coefficient), which includes treatment, time, and time interaction. The treatment coefficient of time interaction provides an estimate of the effect of Baduanjin intervention. The magnitude of the treatment effect will be calculated for each follow-up time point. If there is a statistically significant treatment effect at any point in time, we will also calculate the number of treatments (NNT) required to achieve pain recovery.

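### Neither the primary mixed model nor the per-visit tests condition on baseline VAS, so precision is given up; the estimate stays unbiased and the size of the loss is uncertain

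*Protocol article*

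**What the plan says.** Section 2.2 of the protocol article sets the measurement times: "Primary and secondary outcomes will be measured at baseline, 8, 16 and 24 weeks after intervention, and the next 4 weeks". Section 2.16.1 defines the primary outcome as the VAS change from baseline to week 24, and section 2.3 admits only patients scoring above 40 mm on the 100 mm scale.

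Two kinds of efficacy analysis are described.

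- **Per-visit tests.** The abstract attaches an independent t-test to the VAS change ("by independent t are tested groups"). Section 2.21 says that Student's t or the "Mann-Whitney *U* test will be used to analyze the difference between the intervention group and the control group at each time period".
- **Mixed model.** Under the label of primary analysis, section 2.21 specifies a random-intercept linear mixed model "which includes treatment, time, and time interaction", and then: "The treatment coefficient of time interaction provides an estimate of the effect of Baduanjin intervention".

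The article nowhere mentions baseline VAS as a covariate, analysis of covariance, or a common baseline mean for the two arms.

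**The concern.** Randomisation makes the expected baseline means equal. A model that contains baseline as an outcome visit, with a free treatment difference at that visit, spends information on estimating a difference known to be zero in expectation. The week-24 interaction then subtracts the observed baseline difference in full, which over-corrects whenever the slope of follow-up on baseline is below 1. A test on raw follow-up scores makes the opposite error and corrects for none of it. In both cases the confidence interval is wider than the data require, and a chance baseline imbalance is handled less well than by adjustment.

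This has some weight in a trial of 90 patients. The planning effect comes from an 8-week trial with a different control, and the Discussion lists both differences as limitations, so the true effect may not match the planned one. The model terms are written out, so this is a stated choice and not a detail left open.

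**Working it through.** **Step 1. Reproduce the sample size (section 2.7).** Inputs: 2.37 ± 1.7 against 3.70 ± 1.39, alpha 0.05 (two-sided assumed), power 95%, loss 20%.
- Difference = 3.70 − 2.37 = 1.33.
- Pooled SD = √((1.7² + 1.39²)/2) = 1.553, so d = 1.33/1.553 = 0.857.
- n per arm = 2 × (1.960 + 1.645)²/0.857² = 35.4, rounded up to 36.
- 36/0.8 = 45 per arm. The article's figure is reproduced.

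**Step 2. What the stated model estimates.** Take time as categorical with five levels (baseline and weeks 8, 16, 24 and 28), a random intercept, complete data, unit SD and 36 per arm. The generalised least-squares variance of the week-24 interaction equals that of the difference in mean change, 2 × 2(1 − rho)/36. Constraining the arms to a common baseline mean gives a smaller variance.

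| rho (assumed) | Stated model | Difference in mean change | Common baseline mean | Ratio, stated to constrained |
|---|---|---|---|---|
| 0.3 | 0.0778 | 0.0778 | 0.0506 | 1.54 |
| 0.5 | 0.0556 | 0.0556 | 0.0417 | 1.33 |
| 0.7 | 0.0333 | 0.0333 | 0.0283 | 1.18 |

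**Step 3. General formula.** Let s0² be the baseline variance, β the slope of follow-up on baseline, and σe² the residual variance. In large samples:
- Var(change)/Var(adjusted) = 1 + s0²(1 − β)²/σe².
- Var(follow-up)/Var(adjusted) = 1 + s0²β²/σe².

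With equal SDs, β = rho and σe² = s0²(1 − rho²). The two ratios become 2/(1 + rho) and 1/(1 − rho²). The first gives the last column of the table. The second gives 1.10, 1.33 and 1.96 at rho 0.3, 0.5 and 0.7.

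**Step 4. Effect of the entry threshold.** Assume an unselected VAS that is normal with mean 50 and SD 20, and that the entry VAS is the baseline. Truncation at 40 mm (0.5 SD below the mean) multiplies s0² by 1 − 0.5 × 0.509 − 0.509² = 0.486 and leaves β and σe² unchanged. The change-score ratio becomes 1 + 0.486 × (1 − rho)/(1 + rho):
- rho 0.3: 1 + 0.486 × 0.538 = 1.26
- rho 0.5: 1 + 0.486 × 0.333 = 1.16
- rho 0.7: 1 + 0.486 × 0.176 = 1.09

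Here rho is the correlation in the unselected population. At rho 0.5, 45 per arm analysed by change is worth 45/1.333 ≈ 34 adjusted without truncation, and 45/1.162 ≈ 39 with it.

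**Step 5. Power with 36 evaluable per arm.** Section 2.7 labels its values as changes, so 1.553 is taken as the SD of change. Power ≈ Φ(d√(36/2) − 1.960), with d multiplied by the square root of the variance ratio when adjusted.
- Planned effect, unadjusted: Φ(3.634 − 1.960) = 95.3% (94.8% by the noncentral t), at any rho.
- Planned effect, adjusted, rho 0.5: 98.7% at ratio 1.33; 97.5% at ratio 1.16.
- Half the planned effect (assumed), rho 0.5: 44.3% unadjusted; 55.5% adjusted at ratio 1.33; 50.0% at ratio 1.16.

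**The case against.** The strongest defence is that change from baseline with a treatment-by-time mixed model is a common and valid choice. It already uses baseline by subtraction, and it meets the planned power on the article's own inputs. All of that stands. What remains is that subtraction fixes the slope at 1, which is less efficient than estimating the slope whenever it differs from 1.

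A second defence is that covariates belong in a fuller plan. That would hold if the article were silent, but section 2.21 lists the terms and names the coefficient to be reported.

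The time coding is not stated. The singular coefficient could mean a linear slope, in which case the exact equality in step 2 would not apply. The promise of an effect at each follow-up point favours categorical time.

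A reader might also infer four stronger points, which the article does not support:
- **That regression to the mean after entry above 40 mm makes the loss worse.** Under a linear model with entry VAS as baseline, truncation shrinks s0² and so reduces the loss (step 4). If a separate screening VAS were used, with an assumed correlation of 0.8 with baseline, the ratios would be about 1.40, 1.28 and 1.20: lower than 1.54 and 1.33 at rho 0.3 and 0.5, and only slightly above 1.18 at 0.7.
- **That the t-tests use no baseline value.** The abstract and section 2.16.1 point to a test on change, which uses baseline by subtraction.
- **That power falls below target, for example to about 86% at rho 0.3.** This requires the planning SD to be that of scores. Section 2.7 labels the values as changes. The label is open to doubt because the control value is the larger, but the article does not establish the other reading.
- **That the result is biased.** Randomisation prevents this.

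**Conclusion.** The point holds as a loss of efficiency of uncertain size. The plan's estimate is not biased, and its type I error is intact.

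Relative to adjustment, the change-score variance is inflated by 18% to 54% for rho between 0.7 and 0.3 with equal SDs, and by about 9% to 26% if the entry threshold narrows the baseline spread as assumed. The equal-SD figures are better read as near an upper figure for this trial. At rho 0.5, adjustment would shorten the standard error by about 13% (1 − 1/√1.333) or about 7% (1 − 1/√1.162) respectively. If raw follow-up scores are tested instead, the equal-SD inflation runs from 10% to 96% over the same range of rho.

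At the planned effect the gain in power is small. The practical benefit is a narrower confidence interval, less dependence on chance imbalance, and more power if the true effect is smaller than planned. These sizes rest on assumed values of rho, on the assumed distribution of VAS before selection, and on categorical time with baseline as a level.

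**What to change.** In section 2.21, model VAS at weeks 8, 16, 24 and 28 with fixed effects for baseline VAS, baseline-by-visit, treatment, visit and treatment-by-visit. Alternatively, keep baseline as an outcome visit and constrain the two arms to a common baseline mean. Name the adjusted week-24 difference as the primary estimate. Treat the Pain Disability Index, Quebec scale, SF-36 and RMDQ in the same way, each with its own baseline.

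The cost is about one line of model specification. The baseline values are already collected, no visits or patients are added, and the mixed-model procedure in SPSS can fit the covariate version. The change should be written down before the group codes are opened, so that the choice of covariate cannot be attributed to the results.

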Our research has many advantages. First of all, All Baduanjin are personally guided by professional teachers of more than 5 years to improve the quality of experimental data. Second, we will not only assess pain intensity, but also clinical relevance, quality of life, level of disability, and overall assessment. Third, the intervention effect of each recorded time point was analyzed statistically, build a hybrid linear model, to provide basic data for the treatment course and training frequency of Baduanjin. Fourth, economic evaluation is included for the first time to provide data for the urban benefit of Baduanjin. Fifth, safety index evaluation is included for the first time to verify the safety of Baduanjin training. However, our research also has some limitations. First of all, our sample size calculation may be overestimated. According to previous study, the duration of treatment was only 8 weeks, while ours was 24 weeks. Secondly, the control group used in the study is different from ours, which may affect the results of the study. Finally, the daily activity of the patients in the control group could not be quantified. After the inclusion of the patients, we could only see those with significantly increased or decreased daily activity, and carried out elimination management, but we could not make quantitative comparison with the patients in the intervention group.

Despite its limitations, the results of this trial are expected to provide evidence for the efficacy, safety and economic benefits of Baduanjin in the treatment of chronic low back pain. To provide medical staff, medical staff and patients with long-term exercise therapy plan recommendations.

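### The number needed to treat is calculated only after a significant result at some visit, which makes it too favourable if the true effect is smaller than planned

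*Protocol article*

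**What the plan says.** The primary endpoint, under Outcome indicators, is the "change in VAS score of pain from baseline to the completion of the intervention (week 24"). It is continuous and has one time point.

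The Statistics section compares the groups "at each time period (8 weeks after the intervention, 16 weeks, and 24 weeks or 4 weeks of follow-up"), so there are four post-baseline occasions. It then adds a linear mixed model for several outcomes. Two consecutive sentences follow:

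- "The magnitude of the treatment effect will be calculated for each follow-up time point". This carries no condition.
- "If there is a statistically significant treatment effect at any point in time, we will also calculate the number of treatments (NNT) required to achieve" recovery from pain. This is conditional.

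The conditional sentence does not say which outcome must be significant, in which direction, or at which visit the NNT is then read. The Discussion lists as a strength that "we will not only assess pain intensity, but also clinical relevance".

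**The concern.** An NNT that appears only after a significant test is estimated in a selected set of trials. In those trials the observed difference is, on average, larger than the true one, so the risk difference is too large and the NNT too small. The condition can be met at any of four visits, while the primary endpoint belongs to one of them. As worded, it could also be met by an outcome other than pain, because the preceding sentences cover function, disability and overall effect as well.

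Clinicians tend to read an NNT directly as the size of the benefit. If the effect is modest, the published NNT would flatter Baduanjin. If nothing is significant, no NNT would appear at all, although a wide interval that includes no benefit would then be the informative result.

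**Working it through.** **1. The plan's own figure.** The protocol states no NNT or recovery rate. The only figure that can be reproduced is the sample size (Sample size calculation): 2.37 (SD 1.7) against 3.70 (SD 1.39), α = 0.05, power 95%, loss 20%.

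- Pooled SD = √((1.7² + 1.39²)/2) = 1.553; difference = 1.33.
- n per group = 2 × (1.960 + 1.645)² × 1.553² / 1.33² = 35.4, rounded up to 36.
- 36 / 0.80 = 45 per group, as stated.

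On the 100 mm scale this is a difference of 13.3 mm with an SD of about 15.5 mm.

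**2. How often the condition is met with no true effect (one outcome, either direction).** If the four tests were independent: 1 − 0.95⁴ = 18.5%. Simulated with between-visit correlation 0.5 and 0.8: 16.0% and 11.4%. About half of these favour Baduanjin.

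**3. True NNT under stated assumptions.** From the protocol: 45 per arm, SD 15.5 mm, and control mean 37 mm (3.70 × 10, read as a score). Assumed: normal scores, a constant effect over four visits, correlation 0.6 between visits, and recovery as VAS ≤ 20 mm. With true difference d, the risk difference is Φ((20 − 37 + d)/15.5) − Φ((20 − 37)/15.5).

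- d = 3 mm: 0.183 − 0.136 = 0.047, NNT about 21.
- d = 5 mm: 0.219 − 0.136 = 0.083, NNT 12.
- d = 13.3 mm: 0.406 − 0.136 = 0.269, NNT 3.7.

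**4. NNT reported under the rule.** Each simulated trial has a two-sided t test at 5% at each visit, and an NNT is reported if at least one visit is significant in favour of Baduanjin. The reported NNT is 1 / (mean risk difference in those trials).

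| True difference | True NNT | Favourable condition met | NNT at week 24 | NNT at most significant visit |
|---|---|---|---|---|
| 0 mm | none | about 7% | about 15 | about 9 |
| 3 mm | 21 | about 33% | about 11 | about 8 |
| 5 mm | 12 | about 59% | about 9 | about 6.7 |
| 13.3 mm | 3.7 | over 99% | 3.7 | 3.2 |

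These come from 100,000 simulated trials per row. With only 5,000 trials, the no-effect value at week 24 varies between about 14 and 16.5. Without the condition, the week-24 figure returns the true NNT in the 3 mm, 5 mm and 13.3 mm rows.

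**5. A second set of assumptions.** Here there are 36 completers per arm, a responder improves by at least 2 points on a 0 to 10 scale, the control mean change is 1 point, and the correlation is 0.5 to 0.8. NNT at week 24:

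- planned effect: true 3.1, reported about 3.1;
- half the planned effect: true 6.5, reported 5.0 to 5.5;
- a quarter: true 13.7, reported 6.2 to 7.4;
- no effect: reported 7 to 10.

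The pattern is the same: no bias at the planned effect, and growing bias below it.

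**6. Narrowing the condition does not help.** In the second set, at half the planned effect, requiring significance at week 24 itself and reading the NNT there gives about 4.3 for a true 6.5. That is further from the truth than under the rule as written. The condition itself has to go.

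**The case against.** **The NNT is an add-on.** The primary endpoint, its test and the sample size do not depend on it. This stands, and it limits the weight of the point.

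**Other measures are reported without condition.** A reader might infer from the Discussion's remark on clinical relevance that the NNT is the trial's only such measure. The document does not support that. Overall Perceived Effect, the patient's own rating of change, is an unconditional secondary outcome. So are the disability and quality-of-life scales, and the effect size is calculated at every visit. The Dissemination section also promises results whatever their size or direction. A null trial would still report its effects; only the NNT would be missing.

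**At the planned effect there is no bias.** This is correct for the NNT at week 24, so it would be wrong to say that the reported NNT is overstated in general, or that it appears only when chance favours Baduanjin: a real effect of the planned size meets the condition almost always. But the Discussion itself concedes that the source study was shorter and used a different control group. A reporting rule should not be sound only if the hoped-for effect is true.

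**The larger distortions need a choice the text does not make.** The values of 6.7, 8 and 9 arise only if the NNT is taken at the most significant visit. The text does not prescribe this, though it does not exclude it.

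**Pain recovery has no cut-off in the article.** The only VAS threshold is for entry ("pain and discomfort were over 40 mm on the 100 mm Visual Analog Scale (VAS")). A reader might infer that recovery can be defined after the data are seen. The document does not show this: a responder definition for a supplementary measure is commonly left to the analysis plan, which is not at hand. It is not counted as a fault here.

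**Conclusion.** The concern holds for the conditional reporting alone. The protocol states a rule that produces the NNT only after significance at any of four visits and ties it to none of them. If the true effect is about as large as planned, this does no harm at week 24. If it is clearly smaller, the NNT is too favourable: about 9 for a true 12 and about 11 for a true 21 in the first model. With no effect, a favourable NNT of roughly 15 would be reported in about 7% of trials.

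The direction of the bias follows from the rule. Its size rests on the assumed correlation, recovery cut-off, normality and constant effect, none of which the protocol gives, and on reading the sample-size means as VAS scores, although that section calls them changes.

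**What to change.** Replace the conditional sentence with: *The proportion with pain recovery at week 24 will be compared between the groups in all randomised patients, whatever the significance of the mean difference, and the risk difference and NNT will be reported with 95% confidence intervals; other visits are descriptive.* Point to a recovery definition fixed before database lock, in the analysis plan if it is not already there. Where the interval for the risk difference includes zero, show that interval beside the NNT, because the NNT interval then runs through infinity.

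The cost is wording only: no new data, no more patients, and no change to the primary analysis. The downside is that the reported NNT will usually be less favourable and its interval may include no benefit.
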